### Outcomes

#### Primary outcomes

Hb, ferritn and CRP levels at Day 7

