### Statistics

To demonstrate equivalence of the interventions in restoring Hb levels at Day 7 with 90% power at 5% significance (α = 0.025), 116 women need to be recruited to each intervention group. Based on similar studies, this assumes an acceptable difference in Hb of 1 g/dL and an expected difference of 0.7 g/dL [2, 8, 12]. Hence, the final sample size, accounting for a 10% loss to follow up, is a total of 250 women.

Participants experiencing adverse reactions will remain in the trial unless they fail to meet inclusion and exclusion criteria at any point. Data will be analysed according to the intention to treat principle. Primary outcomes and secondary binary outcomes will be analysed using one sided and two group t-tests. The incidence of adverse reactions and symptom scores will be assessed by calculating rates and 95% confidence intervals. Validity of the Post Partum Symptom Scale (PPSS) will be determined at the time of analyses as part of an embedded study and if validated, correlations between subscales and primary outcomes will be analysed.

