### Follow up

The follow up period consists of 4 weeks with face-to-face visits at Day 7, 14 and 28. At each of these visits women will be seen by a research midwife or doctor. Hb, ferritin and CRP will be checked and results recorded in the study file. Patients will have been discharged with completed pathology forms to facilitate compliance with follow-up laboratory testing. Women will also undergo a clinical examination following a specified checklist to assess for any features of infection or other adverse outcomes . Symptom scores using the three specified scales will be collected at each of the follow up sessions. Research midwives will make all effort to ensure compliance with follow up and can facilitate home visits, including pathology collections if required.

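### The named test for Day 7 haemoglobin, a plain two-group t-test, ignores the other scheduled haemoglobin values, so under the planned 10% loss its 2.5% error relies on loss not biasing the arms differently

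*Protocol article*

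**What the plan says.** The Primary outcomes section lists "Hb, ferritn and CRP levels at Day 7". The sample size rests on Hb alone.

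The Statistics section makes four linked statements:

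- The size: "with 90% power at 5% significance (α = 0.025), 116 women need to be recruited to each intervention group".
- The planning values: "this assumes an acceptable difference in Hb of 1 g/dL and an expected difference of 0.7 g/dL".
- The allowance for loss: the final size, "accounting for a 10% loss to follow up, is a total of 250 women".
- The analysis: "Data will be analysed according to the intention to treat principle", and "Primary outcomes and secondary binary outcomes will be analysed using one sided and two group t-tests".

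Table 1 schedules Hb at enrolment and at Days 7, 14 and 28. The Follow up section matches it: "The follow up period consists of 4 weeks with face-to-face visits at Day 7, 14 and 28". The same section lets research midwives arrange home visits and take blood at home. The Design section states that the trial is open-label.

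**The concern.** A two-group t-test on Day 7 Hb takes one number per woman. It uses neither her enrolment value nor her Day 14 or Day 28 value. The sample was enlarged for loss, which suggests that lost women are expected to supply no Day 7 value. A woman who misses Day 7 but is seen a week later would then drop out of the comparison, although she was randomised and has a relevant measurement.

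The design leaves little room for this. Iron is expected to be 0.7 g/dL worse against a margin of 1.0, so the slack is 0.3 g/dL. Women know their treatment, and how they feel could affect attendance differently in the two arms. If iron-arm women with low Hb are the ones missed, the mean of those who remain flatters iron, and non-inferiority can be declared falsely more often than the stated 2.5%.

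**Working it through.** **Inputs from the article.** Margin 1.0 g/dL, expected deficit 0.7, one-sided α 0.025, power 90%, 116 per arm, 250 in total, 10% loss.

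**Assumed.** The SD (none is given), how Hb differs between lost and retained women, the correlations between visits, and the share of women who return after a missed Day 7.

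**1. The plan's own figure.** Solving the non-inferiority formula for the SD that gives 116 per arm:

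SD = 0.3 × √(116/2) / (1.960 + 1.2816) = 0.705 g/dL.

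So 116 is reproduced only with an SD of about 0.70. Because that value is back-solved, SD 1.5 is shown beside it.

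**2. Standard error after loss.** 250 × 0.9 = 225, or 112.5 per arm.

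- SD 0.705: SE = 0.705 × √(2/112.5) = 0.0940.
- SD 1.5: SE = 1.5 × √(2/112.5) = 0.200.

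**3. False non-inferiority if lost women are left out.** Let the true deficit among all randomised women equal the margin. Then

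bias = loss(iron) × gap(iron) − loss(RBC) × gap(RBC), and error = Φ(bias/SE − 1.960),

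where the gap is how much lower Hb is in lost than in retained women.

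| Pattern of loss | Bias (g/dL) | SD 0.705 | SD 1.5 |
|---|---|---|---|
| 10% per arm, no gap, or the same gap in both arms | 0 | 2.5% | 2.5% |
| 10% per arm, gap 0.5 in iron arm only | 0.05 | 7.7% | 4.4% |
| 10% per arm, gap 1.0 in iron arm only | 0.10 | 18.5% | 7.2% |
| 5% iron, 15% RBC, gap 0.5 in both | 0.025 − 0.075 = −0.05 | 0.6% | 1.4% |

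Example: 0.05/0.0940 = 0.532, and Φ(0.532 − 1.960) = 7.7%. Biases of 0.05 and 0.10 are 17% and 33% of the 0.3 slack.

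The iron-only gap that doubles the error to 5% is (1.960 − 1.645) × SE / 0.10. That is about 0.30 g/dL at SD 0.705 and 0.63 g/dL at SD 1.5.

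**4. What a longitudinal model recovers.** This was simulated with 125 per arm, true deficit 1.0, SD 0.705, about 10% missing Day 7, iron-arm missingness driven by Day 14 Hb, and Day 7–Day 14 correlation 0.6 to 0.8. Leaving out women without a Day 7 value gave about 6% to 11% false non-inferiority. A model that also uses Day 14 Hb gave:

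- about 2.6% if every woman who missed Day 7 was seen at Day 14;
- up to about 6% if half were;
- almost no improvement if none were.

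In the last case only enrolment Hb is left. With enrolment–Day 7 correlation ρ, adjustment changes the error to Φ((bias/SE) × √(1 − ρ²) − 1.960). For ρ from 0.4 down to 0.2, 7.7% becomes 7.0% to 7.5%, and 18.5% becomes 16.2% to 17.9%.

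**5. Precision.** With a share q of the missing women seen at Day 14, effective n per arm = 1 / [(1 − ρ²)/112.5 + ρ²/(112.5 + 12.5q)]. For ρ between 0.6 and 0.8 this is about 117 to 120 if q = 1 and about 115 to 116 if q = 0.5, against 112.5 for the t-test.

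**The case against.** The strongest reply is that the article names a test, not an analysis set. It nowhere confines the analysis to women with a Day 7 blood test, a t-test can follow imputation, and missing-data handling is commonly left to a full protocol or analysis plan, neither of which is shown. This stands. A reader might infer that the plan fixes a completers-only analysis and so contradicts its intention-to-treat label. The text does not support that. Enlarging the sample for loss points that way but is only an inference, and the absence of a missing-data policy from an article is no finding. What remains is narrower: the method that the article does name makes no use of Hb values that the trial will already hold.

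Second, the error figures follow one assumed direction. Nothing in the article says that lost iron-arm women will have lower Hb while lost transfusion-arm women will not. This also stands, which is why the neutral and reversed patterns are in the table.

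Third, home visits and home blood collection are aimed at just the woman who is too unwell to attend, and the 10% is a planning allowance, not a forecast of missed Day 7 samples. They reduce the risk, although the plan still budgets for the loss.

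Fourth, the model cannot rescue women who are lost altogether, and its gain in precision is modest; power at 112.5 per arm is already about 89%. Both are true. They limit what the model can be said to achieve, and they make the tipping-point analysis a necessary part of the change.

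**Conclusion.** The point holds as a cheap improvement, not as the correction of an outright error. The named t-test leaves the enrolment, Day 14 and Day 28 Hb values unused. If women without a Day 7 value are simply left out, the 2.5% error is assured only when loss does not bias the arms differently.

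The size depends on the mechanism. With 10% loss and a gap in the iron arm only of 0.5 or 1.0 g/dL, the error is 7.7% or 18.5% at SD 0.705, and 4.4% or 7.2% at SD 1.5. A reader might take these as the expected error, or conclude that 10% loss in itself inflates it. Neither follows: with equal bias in both arms the error stays at 2.5%, and with the reverse pattern it falls below. The SD is back-solved, and the gaps, correlations and return shares are assumptions.

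The firm gain from changing the method is that it uses women who miss only Day 7 and adds some precision. Protection against bias extends only as far as those women are seen later.

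**What to change.** In the Statistics section, take the primary Day 7 Hb contrast from a longitudinal model of Hb at enrolment and Days 7, 14 and 28. Constrain the arms to a common baseline mean, use an unstructured covariance, and include every randomised woman with any Hb value. Compare the confidence bound for the Day 7 contrast with the 1 g/dL margin.

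Add one tipping-point analysis that lowers the missing iron-arm values step by step until non-inferiority is lost, and report how large that shift is. This is the safeguard for women who are fully lost. Keep the two-group t-test as a sensitivity analysis.

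The cost is a sentence or two in the plan and a little more analysis work, with no new visits, blood tests or participants. The downside is that the model assumes data are missing at random; the tipping-point analysis shows how far the conclusion depends on that.

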### Hypothesis

Intravenous iron is non-inferior to RBC transfusion in women with acute post partum anaemia in correcting Hb levels and improving clinical symptoms with no increased rate of adverse outcomes.

Intravenous iron is superior to blood transfusion in replenishing pre-pregnancy iron stores.

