### Secondary outcomes

Hb, CRP, ferritin and reticulocyte count at Day 14 and 28clinical symptoms at day 7, 14 and 28breastfeeding quality at day 7, 14 and 28adverse reactions

Quantifying CRP will ensure changes to ferritin levels are not the result of an acute phase response. Reticulocyte count will be used as a marker of bone marrow response [19, 20].

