### Procedures, recruitment and randomisation

Table 1 describes the schedule of enrolment, interventions and assessments during the trial.

**Table 1 Tab1:** Schedule for enrolment, interventions and assessments

	Enrolment	Allocation	Post Allocation				Close-out
TIMEPOINT	Feb 2016	At Enrolment	0-48 h	Day 7	Day14	Day 28	Day 28
ENROLMENT:							
Eligibility screen	X						
Informed consent	X						
Randomisation		X					
Intervention/Preparation (pharmacy/blood bank)			X				
INTERVENTIONS:							
RBC Transfusion			X				
Intravenous Iron Polymaltose			X				
ASSESSMENTS:							
E-5D,MFI-20) and PPSS symptom scores			X	X	X	X	
Clinical history and examination	X		X	X	X	X	
Hb	X			X	X	X	
Ferritin	X			X	X	X	
UEC	X						
CRP	X			X	X	X	
Reticulocyte Count	X			X	X	X	
Group and hold	X						
Vital Signs		X		X	X	X	

Clinical staff at all sites will be able to contact the research team at any time to enrol participants. Research midwives at the primary site will identify women from daily birth records who have had a PPH >1000mls. These women will be briefed on the study using a structured information sheet about the trial and interventions. Following this they will verbally consent to preliminary bloods including a group and hold, haemoglobin, creatinine (to exclude acute kidney injury), ferritin and CRP. Eligible patients will then provide written informed consent and be enrolled to participate in the study (intervention and follow up phases).

Participants will be stratified as per mode of delivery and randomisation will occur within these groups by a computer generated list, blocked in a 1:1 ratio to each intervention. A central telephone service will be accessed to allocate the intervention and study identification number.

Eligible women who decline partipation in the trial will be offered 325 mg oral ferrous sulphate daily until iron replete, which is in accordance with current standard practice guidelines. This will be mentioned in the consent process.

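### Unadjusted t-tests are the only analysis named for Day 7 ferritin and CRP; if these are right-skewed and tested untransformed, power for modest effects is lost, chiefly for CRP.

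*Protocol article*

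**What the plan says.** Under Primary outcomes the protocol article lists "Hb, ferritn and CRP levels at Day 7". Under Statistics it says: "Primary outcomes and secondary binary outcomes will be analysed using one sided and two group t-tests". No other test, scale or covariate is given for any of the three.

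The sample size passage in the same section is about Hb alone: "with 90% power at 5% significance (α = 0.025), 116 women need to be recruited to each intervention group", where "this assumes an acceptable difference in Hb of 1 g/dL and an expected difference of 0.7 g/dL". No spread, margin or power is stated for ferritin or CRP.

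CRP also has an interpretive job. Under Secondary outcomes: "Quantifying CRP will ensure changes to ferritin levels are not the result of an acute phase response". For ferritin, the Hypothesis section states a direction: "Intravenous iron is superior to blood transfusion in replenishing pre-pregnancy iron stores". The Primary objectives section speaks of non-inferiority for the same aim.

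Table 1 shows that ferritin and CRP are both measured at enrolment, so a baseline value exists for each woman.

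**The concern.** A single test is assigned to three outcomes of different kinds. Hb in a narrow eligibility range is well served by a difference in means. Ferritin and CRP cannot fall below zero. If they have a long upper tail, a few very high values dominate both the arm means and the standard error.

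Two things are at stake. First, the t-test may miss a modest difference that a log-scale analysis of the same data would find. Second, a difference in arithmetic means may describe the typical woman poorly. For CRP the first point bears on interpretation: if a modest difference in CRP between arms goes undetected, an acute phase contribution to the ferritin result may be dismissed too readily.

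**Working it through.** **Inputs from the article.** "the final sample size, accounting for a 10% loss to follow up, is a total of 250 women", and allocation is "blocked in a 1:1 ratio to each intervention". So 250 × 0.9 = 225 women with data, and 225 / 2 = 112.5, taken as 112 per arm. One-sided level 0.025; critical t on 222 df = 1.971.

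**The plan's own figure.** There is none for ferritin or CRP. The 116 per group concerns Hb and states no SD. It implies SD = (1 − 0.7) × √(116/2) / (1.960 + 1.282) = 0.705 g/dL. It has no bearing on this point.

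**Assumed.** Log-normal values, the same log-SD (s) in both arms, no covariate. Because the article gives no spread, a range is shown.

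**Power on the log scale.** Noncentrality = ln(r) / (s × √(2/112)), with √(2/112) = 0.1336. For r = 1.4, ln(r) = 0.3365:

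- s = 0.8: 0.3365 / 0.1069 = 3.147, power 88%
- s = 1.0: 0.3365 / 0.1336 = 2.518, power 71%
- s = 1.2: 0.3365 / 0.1604 = 2.098, power 55%

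**Power on the original scale.** Found by simulation (8,000 to 40,000 trials per setting), which also reproduces the log-scale values:

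| True ratio | log-SD | Original scale | Log scale |
|---|---|---|---|
| 1.4 | 0.5 | 99.7% | 99.9% |
| 1.4 | 0.8 | 77% | 88% |
| 1.4 | 1.0 | 51–52% | 71% |
| 1.4 | 1.2 | 33% | 55% |
| 2 | 0.8 | 100% | 100% |
| 2 | 1.0 | 97% | 99.9% |
| 2 | 1.2 | 86% | 99% |

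The first row shows little loss partly because both tests are near their ceiling. With 116 per arm and the ratio chosen so that the log-scale test has about 90% power, the original-scale test has 86% at log-SD 0.5, 79% at 0.8, 72% at 1.0 and 64% at 1.2.

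**One-sided error, equal means, equal log-SD.** With 112 per arm and log-SD from 0.5 to 1.2, each tail of the original-scale test lies between 2.1% and 2.6%. That is near nominal, or slightly conservative at the wider spreads.

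**One-sided error, equal means, wider iron arm.**

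| log-SD, transfusion v iron | Falsely iron higher | Falsely iron lower |
|---|---|---|
| 0.6 v 1.0 | 0.9% | 5.3% |
| 0.8 v 1.2 | 0.8% | 5.9% |

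A Welch test gives practically the same tails, because with equal arm sizes the two t statistics coincide.

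**Non-inferiority boundary.** The article gives no ferritin margin. With an assumed margin of 20% of the mean, equal log-SD and 116 per arm, the false-positive rate is 2.8% to 3.4% for log-SD 0.5 to 1.5.

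**The case against.** The strongest reply is that the article never says the values will be left untransformed. A t-test of logged values is still a t-test, and scale is often settled in an analysis plan, which is not shown. This stands in part. The original scale is the natural reading of an unqualified t-test on levels, but it is an inference, and silence about a transformation is not itself an error. What remains is that the only method named is unadjusted and applied alike to all three outcomes, although a better one is available at little cost.

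A second reply is that the ratio of 1.4 is arbitrary. The arms receive very different amounts of iron, so the ferritin ratio may be far larger. At a ratio of 3 the original-scale test has about 99% power or more throughout the range shown. This stands for ferritin, and is why the point bears mainly on CRP.

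A reader might go further and infer that the one-sided error rates are simply wrong. The documents do not support that. If values vary in proportion to their level, the log-SD is the same in both arms, and a test of equal means is close to 2.5% in each tail. The error is clearly distorted when log-scale spread differs by arm. That is plausible for ferritin after intravenous iron, but the article does not show it and offers no reason to expect it for CRP. With a wider iron arm, the inflated tail is the one that declares iron lower; for the stated superiority hypothesis the test is conservative.

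Nor do those unequal-spread cases argue for the log scale. With equal arithmetic means and log-SD 0.6 v 1.0, the log-scale test rejects about 82% of the time, because the geometric means differ. It is answering another question.

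Finally, the t-test sentence covers primary outcomes and binary secondary outcomes. Carrying the criticism to Day 14 and Day 28 ferritin and CRP would be conjecture.

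**Conclusion.** The point holds as one of efficiency and interpretability. If ferritin and CRP are roughly log-normal with log-SD 0.8 to 1.2 and are tested untransformed, the named t-test gives up about 11 to 22 percentage points of power at a true ratio of 1.4. The loss is negligible at log-SD 0.5, and at a ratio of 2 it is at most about 13 points (log-SD 1.2). The consequence is greatest for CRP.

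The size depends wholly on spreads and effects that the article does not give. The Hb comparison and its sample size are unaffected. A general claim of invalid one-sided error is not part of this conclusion. The improvement is worth making before outcome data are seen, since choosing a transformation afterwards for two primary outcomes in an open-label trial would invite doubt.

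**What to change.** In Statistics, keep the original scale for Hb. State that Day 7 ferritin and CRP will be analysed on the log scale, by a linear model with treatment arm and the log of the enrolment value as covariate, reported as ratios of geometric means with 95% CI.

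The cost is a sentence or two of wording and no extra data. The real trade-off is the estimand: the result becomes a ratio of geometric means instead of a difference in arithmetic means, and the text should say so. Any ferritin margin would have to be expressed as a ratio, and a rule is needed for CRP results reported as below the assay limit. The gain from the baseline covariate depends on its correlation with Day 7, which the article does not give; it is not counted in the power figures above.

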**Methods/design:**

IIBAPPA is a multi-centre randomised non-inferiority trial. Women with a primary post-partum haemorrhage (PPH) >1000 mL and resultant haemoglobin (Hb) 5.5-8.0 g/dL after resuscitation with ongoing symptomatic anaemia who are otherwise stable (no active bleeding) are eligible to participate. Patients with sepsis or conditions necessitating rapid Hb restoration are excluded. Eligible participants are randomised to receive a blood transfusion or a single dose of intravenous iron polymaltose calculated using the Ganzoni formula. Primary outcome measures include Hb, Ferritin and C-Reactive Protein levels on Day 7. Secondary outcomes evaluate (i) Hb, Ferritin and CRP levels on Day 14, 28, (ii) anaemia symptoms on Day 0, 7, 14 and 28 using structured health related quality of life questionnaires, (iii) treatment safety by assessing adverse reactions and infection endpoints and (iv) the quantitative impact of anaemia on breast feeding quality using a hospital designed questionnaire.

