### Primary objectives

To determine if intravenous iron is non-inferior to RBC transfusion in correcting haemoglobin deficit, replenishing iron stores and improving clinical symptoms in women with acute post-partum anaemia without increasing the rate of adverse outcomes.

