### Secondary objectives

To determine if intravenous iron is superior to RBC transfusion in improving the quality of breast-feeding in women with acute post-partum anaemia.

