### Participants/eligibility criteria

The sample population will consist of women who sustain a primary post-partum haemorrhage in excess of 1000 mL with a resultant Hb drop of ≥3 g/dL and Hb of 5.5-8.0 g/dL. Asymptomatic women, as well as patients with mild signs and/or symptoms of anaemia including dizziness, increased respiratory rate to >/= 25 on minimal exertion, HR 100-130 or a postural blood pressure drop of >10 mmHg are eligible.

Blood loss will be assessed by weighing all blood stained articles including sponges, sheets, under-pads and clothing. If delivery occurs in the operating theatre (after subtracting liquor volume) suction output will be added. Where possible all blood spillage will be mopped up, weighed and added to the total.

Evidence suggests 90% of women with PPH > 1000 mL have resultant Hb < 10 g/dL thereby defining our haemorrhage cut off [1]. Similarly the nominated minimum Hb is a conservative estimate based on levels used in previous studies evaluating expectant management in patients with acute anaemia [6, 10, 11, 17].

If applicable, enrolment must occur within 48 h of resuscitation and stabilisation. Stabilisation is defined as (1) having no active per vaginal bleeding in excess of expected post-partum losses and (2) having all vital parameters within hospital review criteria for a period of 12 h immediately prior to study recruitment (i.e. all patients having pulse <130 bpm, systolic blood pressure > 90 mmHg, diastolic blood pressure < 110 mmHg, respiration rate < 25, temperature < 38.5 degrees and oxygen saturations >90%).

Patients with significant antenatal or peri-partum complications such as severe pre-eclampsia who are now stable (as per above criteria) are eligible. Women who receive whole blood transfusion, other blood products, antibiotics (other than for sepsis) and intravenous fluid therapy prior to stabilisation will also be eligible.

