### Data collection

Each participant will have a study file labelled with their name, medical record number, study identification number and allocated treatment. This will contain copies of their consent forms (the original will remain in their hospital file while they are an inpatient), questionnaires and comprehensive study checklists template for documenting outcome variables and other clinical data. Files will be kept in locked cabinets on the ward and in the principle researcher’s office after discharge and remain on site for 7 years before being destroyed/archived.

Baseline blood results (Hb, ferritin, CRP) for all enrolled participants will be manually transcribed by researchers from the hospital electronic database into the participant’s study file. Once allocated to an intervention, the number and coding sticker of each blood unit or the serial number and dose of the pre-packaged iron infusion will be recorded in the template.

Patient symptoms will be scored on Day 0 prior to receiving any intervention using previously validated HRQoL questionnaires: the EuroQol-5D (E-5D), the Multidimensional Fatigue Inventory (MFI-20) and our in-hospital devised Post-Partum Symptom Score (PPSS).

The EQ-5D measures a patient’s activity level and emotional attitude at a single point in time, indirectly reflecting symptom severity. It consists of five items (Mobility, Self-Care, Usual Activities, Pain/Discomfort and Anxiety/Depression) where a patient scores: 1 = no problems, 2 = more problems, 3 = extreme problems. The sixth item is a patient’s own global evaluation of their health using a visual analogue scale with a range from 0 (worst imaginable health state) to 100 (best imaginable health state) [21].

The MFI is a 20-item self-report instrument designed to comprehensively measure fatigue. It evaluates: general, physical and mental fatigue and reduced motivation and activity. Patients score each dimension on a scale ranging from 4 to 20 where 4 is optimal. Hence, higher scores indicate more severe symptoms. Scales are balanced to reduce the influence of response tendencies. Each scale sub-total is interpreted independently. Questions are structured to evaluate symptoms over a period of time (5-7 days) which is particularly useful to measure treatment impacts [22]. Both the MFI and EQ-5D have previously been validated in pilot studies of obstetric cohorts [23].

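### Symptom scores are to be analysed as rates, and neither symptom non-inferiority nor breastfeeding superiority has a stated comparison between the arms

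*Protocol article*

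**What the plan says.** All places are in the protocol article.

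- **Primary objectives:** "To determine if intravenous iron is non-inferior to RBC transfusion in correcting haemoglobin deficit, replenishing iron stores and improving clinical symptoms". The Hypothesis section repeats the symptom claim. The outcome lists, however, place clinical symptoms among the secondary outcomes.
- **Secondary objectives:** "To determine if intravenous iron is superior to RBC transfusion in improving the quality of breast-feeding". This is the only secondary objective.
- **Statistics, symptoms and safety:** "The incidence of adverse reactions and symptom scores will be assessed by calculating rates and 95% confidence intervals".
- **Statistics, PPSS:** its validity is to be examined when the data are analysed, and "if validated, correlations between subscales and primary outcomes will be analysed".
- **Statistics, tests:** "Primary outcomes and secondary binary outcomes will be analysed using one sided and two group t-tests".
- **Data collection:** for the MFI-20, "Patients score each dimension on a scale ranging from 4 to 20 where 4 is optimal". The EQ-5D has five three-level items and a 0 to 100 visual analogue scale. The PPSS has a seven-question feeding subscale.
- **Who is enrolled:** the abstract describes women "with ongoing symptomatic anaemia who are otherwise stable". The eligibility section admits "Asymptomatic women, as well as patients with mild signs and/or symptoms of anaemia".

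**The concern.** Both objectives ask how iron compares with transfusion. The methods attached to the relevant outcomes do not make that comparison. A rate does not describe a fatigue score or a visual analogue score. A confidence interval supports non-inferiority only if it is an interval for a difference between arms, read against a margin fixed in advance. A correlation between feeding scores and laboratory values does not involve the treatment arm.

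At stake is whether the trial can support two of the conclusions it sets out to draw. Without a pre-stated margin, an absence of visible difference in symptoms could be reported as non-inferiority. Without a stated feeding comparison, the effect measure and time point could be chosen after the data are seen.

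**Working it through.** The point rests on matching objectives to methods, so there is no figure in the plan to reproduce. The stated 116 per group is for Hb at Day 7 only.

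**1. Match each outcome to its stated method.**

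| Outcome | Question asked | Stated method | Does it answer the question? |
|---|---|---|---|
| Hb at Day 7 | Non-inferiority | t-test, margin 1 g/dL | A comparison and a margin are stated |
| Symptom scores | Non-inferiority (part of primary objective) | Rates and 95% intervals | No: no arm difference, no margin, wrong summary for a score |
| Breastfeeding quality (PPSS feeding subscale) | Superiority of iron | Correlation with primary outcomes if validated; possibly also rates and intervals | No: neither is a superiority comparison of arms |
| Laboratory values at Days 14 and 28 | Secondary, continuous | None: not primary, not binary, not a symptom score | No method stated |
| Adverse reactions | Secondary, the only clearly binary outcome | Rates and intervals, and apparently also t-tests | Two sentences overlap |

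**2. Symptoms.** To conclude non-inferiority on a score, the plan needs (a) an effect measure, such as the mean difference of iron minus transfusion, (b) a margin M, and (c) a rule. For the MFI-20, where higher is worse, the rule is that the upper 95% limit lies below +M. For the visual analogue scale, where higher is better, it is that the lower limit lies above −M. The Statistics section supplies none of the three for any symptom score.

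**3. Breastfeeding.** The primary outcomes are Hb, ferritin and CRP at Day 7. Correlating the feeding subscale with them addresses how anaemia relates to feeding, which the abstract does list as an aim. It does not address whether feeding is better after iron than after transfusion. The Follow up section counts three symptom scales and Table 1 names the PPSS among the symptom scores, so the rates sentence may cover it too. That adds a summary but no test of superiority.

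**4. Can the trial support a symptom margin?** Evaluable women after 10% loss: 250 × 0.9 = 225, so 112 per arm (225 / 2 = 112.5). The standard error of a mean difference is SD × √(2/112) = 0.134 SD. The 95% half-width is 1.96 × 0.134 = 0.26 SD. With 90% power, one-sided 0.025 and a true difference of zero (an assumption), the smallest workable margin is (1.96 + 1.28) × 0.134 = 0.43 SD, before any gain from baseline adjustment. The documents give no SD for any score, so this stays in SD units. It shows precision only; it does not justify a margin.

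**5. The t-test on binary data.** Exact type I error of a two-group t-test, 112 per arm, two-sided 5%:

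| True incidence | Type I error |
|---|---|
| 1% | 0.017 |
| 3% | 0.044 |
| 10% | 0.052 |
| 30% | 0.051 |

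The method is misnamed for binary data, but the error rate is close to nominal or conservative.

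**6. Eligibility.** The abstract's description and the eligibility section cannot both hold for asymptomatic women. This determines whose symptoms the comparison describes.

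**The case against.** The strongest reply is that a journal article condenses the plan, and an unseen analysis plan may define the arm difference and margin. The text does not say that the intervals are per arm, and a 95% interval for a difference read against a margin would be a proper non-inferiority analysis. Rates also fit some items: the share of women reporting a problem on an EQ-5D item is a proportion. This stands in part. It does not remove the point, because the article does state methods, and those stated do not fit the MFI-20, the visual analogue scale or the two objectives.

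Several stronger readings are tempting but not supported:

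- **That correlation is the only analysis of the PPSS, or that every PPSS analysis waits on validation.** The PPSS also counts as a symptom score, and the validation condition is attached only to the correlations.
- **That t-tests on rare reactions give misleading p-values.** Adverse reactions are expressly given rates and intervals, the low reaction rates in the Background section are for intravenous iron only, and the t-test is conservative at 1% and 3%.
- **That asymptomatic women dilute the symptom difference by a known amount.** The documents give neither their share nor an expected score difference, so no figure can be put on it.
- **That calling the PPSS previously validated is a material contradiction.** The Data collection wording is loose, but the same sentence calls the scale hospital-devised, and no analysis changes.

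**Conclusion.** The point holds. As stated, the methods give no between-arm effect measure or margin for symptoms and no superiority comparison for breastfeeding. This affects one component of the primary objective and all of the secondary objective. The continuous laboratory outcomes at Days 14 and 28 also have no stated method.

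A reader might infer that the trial cannot answer these questions at all. The documents do not support that: women are randomised and the scores are scheduled at Day 0 and at Days 7, 14 and 28, so the comparisons remain possible. The defect lies in the stated analysis, not in the design or the data. The conclusion assumes that the article's Statistics section reflects the plan to be followed; an analysis plan that already contains the comparisons and a margin would reduce the problem to correcting the published text.

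**What to change.** - **Scores:** replace the rates sentence, as it applies to scores, with a between-arm mean difference and 95% confidence interval for the MFI-20, the EQ-5D visual analogue scale and the PPSS feeding subscale at Days 7, 14 and 28. Adjust for the Day 0 score and for mode of delivery, which is the randomisation stratum.
- **Symptom non-inferiority:** name one symptom score and time point, and state a non-inferiority margin with its justification and the direction of the scale. Without a margin, better modelling still cannot support the claim.
- **Breastfeeding:** state a superiority comparison of arms on the feeding subscale and report it together with the scale's validation status. Keep the correlations as a separate analysis.
- **Secondary outcomes:** correct the t-test sentence. Use t-tests or ANCOVA for the continuous laboratory values at Days 14 and 28, and a risk difference with a score or exact 95% interval for adverse reactions.
- **Eligibility:** reconcile the abstract and the eligibility section on asymptomatic women.

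**Cost:** wording in the protocol and analysis plan, plus the clinical work of justifying one margin. No new visits, instruments or data are needed. It should be settled before arm-level data are seen.
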